### Blinding

2.11

This study uses a single-blind method. Acupuncture and acupuncture pseudo-acupoints will be performed by the same professional acupuncturist in the outpatient department according to uniform standards. All examinations will be checked and evaluated by the same doctor. The subjects will not know the specific grouping situation. Outcome evaluation and data statistics are performed by a third party who is not involved in the treatment. Only in emergency situations, such as a serious adverse event (AE), or when the subject needs emergency rescue, the researcher will report to the supervisor and the principal investigator to decide whether to unblind. Once the subject is unblinded, the case will be regarded as a drop-out case and will not be included in the efficacy analysis. However, if there is an adverse reaction, it should be included in the adverse reaction analysis, and the unblinding should be recorded in the Case Report Forms (CRFs) “Early Subject Exit Page” Related information, including the time of unblindness, reason, treatment, and treatment status.

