### Exclusion criteria

2.7

Patients meeting any of the following criteria will be excluded from the study:

(1)Patients age <7 years or >16 years, patients not suffering from myopia, or patients with myopia and strabismus/amblyopia;(2)myopia related to retinal dystrophies or collagen syndromes, and developmental disorders;(3)subjects with serious systemic diseases, such as cerebrovascular, liver, kidney, hematopoietic system, and psychiatric diseases;(4)use other related drugs or treatments within 2 weeks;(5)Spherical equivalent (SE) < -0.5D, or combined with pathologic myopia-related fundus changes and/or significant visual function impairment;(6)the affected eyes have other diseases that affect the determination of acupuncture efficacy;(7)patients with less than 14 weeks of follow-up, inability to obtain refraction data in the first 14 weeks, patients lost to follow-up, or unable to keep office follow-up at our institution.

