### Informed consent

2.8

Before the study, the general study process and the responsibilities of the participants and researchers will be explained to potential participants or their guardians. Participants or their guardians will be informed that their entry into the trial is entirely voluntary and that they could withdraw at any time. In the event of their withdrawal, data collected on the participant will not be erased and will be used in the final analyses. Written informed consent should be obtained from each participant before he or she undergoes any interventions related to the study.

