### Statistical analyses

2.16

Data analyses will be processed with SPSS 22.0 (SPSS Inc., Chicago, IL) and supervised by a skilled statistician blinded to group allocation.

The Full Analysis Set (FAS) is for all participants who have been randomized in terms of the intention-to-treat (ITT), and the per-protocol analysis set (PPS) and is for the individuals who complete the trial and do not have significant protocol violations. On the basis of rule of the last-observation-carried-forward, missing values will be imputed. In order to evaluate therapeutic effect and safety, the FAS and PPS will be used simultaneously.

Categorical data, such as gender and medical history, will be tabulated with frequencies or percentages; and continuous data, such as age and disease course, will be reported as mean ± standard deviation (SD), or median. For the baseline variables, sociodemographic data and other basic indicators will be carried out using analysis of variance (ANOVA) and χ^2^. To compare variables before and after treatment in the same group, a paired *t* test will be used. Repeated-measures ANOVA will be used to compare the intergroup differences among the 3 groups. Tests of ITT between the acupuncture with the deqi group and acupuncture without the deqi group arms and between the acupuncture withou the deqi group and waiting-list group arms with respect to the change will based on time-intervention interactions in the mixed-effect models. A *P* value of less than .05 (2-sided) indicates a statistically significant difference, with 95% confidence intervals.

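### Two rules that remove participants for events after randomisation contradict the all-randomised analysis set and can bias the efficacy comparison

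*Protocol article*

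**What the plan says.** Two rules in the protocol article take participants out:

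- Section 2.11 (Blinding): "Once the subject is unblinded, the case will be regarded as a drop-out case and will not be included in the efficacy analysis". The code may be broken in a narrow set of circumstances: "Only in emergency situations, such as a serious adverse event (AE), or when the subject needs emergency rescue". The sentence does not say which analysis set it applies to.
- Section 2.7 (Exclusion criteria) opens with "Patients meeting any of the following criteria will be excluded from the study". Item 7 of that list names "patients with less than 14 weeks of follow-up, inability to obtain refraction data in the first 14 weeks, patients lost to follow-up", followed by being unable to attend follow-up at the institution.

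Two other sections keep participants in:

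- Section 2.16 (Statistical analyses): "The Full Analysis Set (FAS) is for all participants who have been randomized in terms of the intention-to-treat (ITT"). Missing values are imputed by last observation carried forward (LOCF). The section adds: "In order to evaluate therapeutic effect and safety, the FAS and PPS will be used simultaneously".
- Section 2.8 (Informed consent), on participants who withdraw: "data collected on the participant will not be erased and will be used in the final analyses".

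**The concern.** An intention-to-treat set protects the comparison because membership is fixed at randomisation. Loss to follow-up, a missing early refraction and emergency unblinding all happen later and may be related to the arm or to the child's course. If such children are removed, the arms being compared are no longer the arms that were randomised.

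Differential removal is plausible here, though not shown. The needling events listed in section 2.14 can arise only in the two acupuncture arms. Waiting-list children receive no acupuncture until the study is complete, so they know they are untreated and may leave for other reasons. The contrast of acupuncture without Deqi against the waiting list is one of the two planned between-arm tests.

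There is also a practical problem. Two analysts could each follow this text faithfully and analyse different children for the primary outcome.

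**Working it through.** **1. The rules side by side**

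| Participant | Sections 2.7 and 2.11 | Sections 2.16 and 2.8 |
|---|---|---|
| Unblinded in an emergency | Out of efficacy (2.11) | In the FAS (2.16) |
| Lost to follow-up | Out of the study (2.7, item 7) | In the FAS with LOCF (2.16); data kept if the child withdrew (2.8) |
| No refraction by week 14 | Out of the study (2.7, item 7) | In the FAS (2.16) |

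No row can satisfy both columns. If item 7 were applied to randomised children, LOCF would also have little left to act on.

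**2. Timing**

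Section 2.10 randomises after eligibility is confirmed and consent signed. At that moment nobody knows a child's length of follow-up, later loss or week-14 data. Only the last clause of item 7, on being unable to attend, can be assessed beforehand.

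The 14-week limit also reaches past treatment. Treatment lasts 3 months, about 13 weeks, and the visit after month 3 is month 6 (section 2.15). If follow-up is counted to the last visit attended, a child with a month-3 refraction and no later visit has under 14 weeks and would be excluded.

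**3. How many children**

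Inputs from section 2.9: 20% loss and 300 participants. The plan's loss step follows from its own 74 per arm: 74 / 0.8 = 92.5, rounded up to 93, and 3 × 93 = 279. (The 74 itself does not follow from the stated inputs; that is a separate matter and nothing here rests on it.)

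Ceiling for item 7: 0.20 × 300 = 60 children. This assumes that the full planned loss occurs and that every loss falls under item 7.

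**4. How far an arm mean could move**

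Let *p* be the share of an arm removed and *d* the mean difference between retained and removed children. Then

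full-arm mean = (1 − *p*) × retained mean + *p* × removed mean,

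so retained mean − full-arm mean = *p* × *d*.

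The benchmark is the planned difference in section 2.9: −1.52 − (−1.81) = 0.29 D. The documents give neither *p* by arm nor *d*, so both are assumed. Removal is from one arm only:

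| *p* | *d* = 0.25 D | *d* = 0.5 D | *d* = 1.0 D |
|---|---|---|---|
| 5% | 0.0125 D (4%) | 0.025 D (9%) | 0.05 D (17%) |
| 10% | 0.025 D (9%) | 0.05 D (17%) | 0.10 D (34%) |
| 20% | 0.05 D (17%) | 0.10 D (34%) | 0.20 D (69%) |

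Percentages are of 0.29 D. For unblinding alone, with an assumed 1% to 2% removed, the shift is 0.01 × 0.25 = 0.0025 D to 0.02 × 1.0 = 0.02 D, or 1% to 7%.

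**5. Two arms together**

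The bias in a difference between arms A and B is *p*A × *d*A − *p*B × *d*B. It is zero when both arms lose the same share with the same difference.

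**The case against.** The strongest reply is that item 7 sits in an eligibility list, that randomisation follows eligibility, and that sections 2.8 and 2.16 show an intention to keep everyone. On that view item 7 is clumsy screening text and not an analysis rule. This may be what was meant, and it is why 60 is only a ceiling. It does not rescue the wording: loss to follow-up cannot be a screening fact. It also leaves section 2.11 untouched, which speaks of the efficacy analysis without limiting itself to the PPS.

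Several stronger readings are tempting, and the documents do not support them:

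- *That the comparison is biased.* Section 2.9 applies its 20% to all arms alike, and nothing in the protocol shows that loss will differ between them. Only "can bias" is justified, as a statement of possibility; any single percentage from the table is an assumed scenario.
- *That every serious adverse event removes a child.* Under section 2.11 such an event leads to a report and a decision on whether to unblind.
- *That harm would be hidden.* Section 2.11 keeps the adverse reactions of unblinded cases in the safety analysis, section 2.14 records events throughout, and section 2.16 analyses safety in the FAS as well. A PPS safety table would be less complete, but it would stand beside the FAS table.
- *That FAS and PPS have equal standing.* Section 2.16 uses both but describes its between-arm mixed-model tests as ITT. The primary set is implied without being named.
- *That the unblinding rule contradicts section 2.8.* That section concerns voluntary withdrawal, so only item 7 conflicts with it.

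**Conclusion.** The contradiction stands on the text. Section 2.11 and item 7 of section 2.7 both remove participants for events after randomisation, while section 2.16 defines the FAS as everyone randomised. Item 7 also conflicts with section 2.8. Following the removal rules as written would give up the protection of randomisation for the primary outcome.

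Item 7 is the larger risk, with a ceiling of about 60 of 300; unblinding probably affects few. The size and direction of any bias cannot be derived from the documents. The range of about 0.01 to 0.20 D rests on assumed one-arm removal of 5% to 20% and an assumed gap of 0.25 to 1.0 D. The 0.29 D benchmark is the protocol's difference between its experimental groups 1 and 2, so it is only a yardstick for the waiting-list contrast.

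**What to change.** 1. Section 2.7, item 7: delete the clauses on length of follow-up, missing refraction and loss. Keep only what can be assessed before randomisation, such as being unable to attend visits.
2. Section 2.11: state that unblinded participants stay in the FAS with all their available data, and that removal for unblinding applies only to the PPS.
3. Section 2.16: state the same for participants who are lost or lack early refraction. Name the FAS, analysed by ITT, as primary for efficacy and the PPS as a sensitivity analysis. Base the safety summary on all randomised participants and not on the PPS.

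The cost is wording, and an estimate that may be slightly less favourable than one in completers. Keeping these children in the FAS does not by itself remove bias from missing data: LOCF would carry their early values forward in place of the later ones that were never measured.

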### Intervention

2.12

#### Basic treatment

2.12.1

The basic treatment includes conventional frame glasses correction treatment. All patients will receive disease health education, including eye hygiene, eye use time, rest time, and health consultation, but in order to avoid the confounding effect of excessive eye use, the research team will not provide special eye health intervention measures.

#### Acupuncture deqi group

2.12.2

On the basis of correction treatment with frame glasses, use acupuncture for acupoint treatment, specific as follows: the patient takes a sitting or supine position, selects eye acupuncture points (Sizukong, Tongziliao, Sibai), local skin and healers who left after routine disinfection 75% ethanol, with the sterile filiform needles (0.25 mm in diameter, 40 mm in length; Hwatuo, Suzhou, China), use both hands to insert the needle, flat puncture to deqi, lift and twist, 20 to 30 min/time.

#### Acupuncture without deqi group

2.12.3

To avoid the deqi response, no needle manipulation will be performed after the perpendicular insertion. In order to reduce the bias caused by performance, all the rest of the clinical procedures remain the same.

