Acupuncture is an ancient therapy with a history of thousands of years and is now widely used in the medical system. Some clinical studies and systematic reviews show that acupuncture is increasingly used in the clinical treatment of many eye diseases, including dry eye syndrome,^[20]^ blepharoptosis,^[21]^ oculomotor paralysis,^[22]^ blepharospasm,^[23]^ and other ophthalmic diseases, and has a good effect.^[24,25]^ In addition, some randomized controlled trials (RCTs) have reported that acupuncture, as an adjuvant therapy, can effectively improve the diopter and vision in the sense of myopic children.^[26,27]^ Deqi is considered to be an important parameter to achieve curative effect in acupuncture treatment in traditional Chinese medicine theory and practice.^[28]^ Deqi is a complex cluster of sensation evoked by acupuncture stimulation, including aching, dull, heavy, numb, radiating, spreading, and tingling.^[29]^ Modern neuroimaging monitors the dynamic response of acupuncture with specific regions to the whole brain.^[30–33]^ Compared with sham acupuncture, verum acupuncture at true acupuncture points is more likely to elicit a sense of de qi, and the acupuncture needle sensations of Deqi and sharp pain are associated with different patterns of activations and deactivations in the brain.^[34,35]^ The concept of Deqi is a long-standing belief to ensure the efficacy of acupuncture in the treatment of myopia, but this belief has not been confirmed by sufficient evidence of RCTs. In the current paper, we designed a randomized, single-blind, large-scale clinical trial to compare the curative effect of acupuncture for Deqi and acupuncture without Deqi in adolescent patients with myopia.

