### Study design

2.2

This clinical study is a parallel-group, randomized controlled, and single-blind study. The experiment will begin in August 2020 and will be completed in August 2023. After obtaining informed consent, 300 eligible adolescents will be recruited and randomly divided into acupuncture Deqi group, acupuncture without Deqi group, and waiting list group. The trial will include a 3-month treatment period and a 9-month follow-up period. All groups will be given frame glasses for corrective treatment; patients in the acupuncture Deqi group will also be treated with acupuncture at acupoints around the eyes to Deqi, while acupuncture without Deqi group will be treated with acupuncture, but no needle manipulation will be performed. The waiting list group will not receive acupuncture treatment. Results will be assessed at 3 points, including baseline, end of acupuncture treatment, and end of follow-up (Fig. 1 flowchart and Fig. 2 visit indicators). The purpose of this study is to objectively evaluate the clinical efficacy of acupuncture at 3 acupoints (Sizhukong, Tongziliao, and Sibai) in adolescents with myopia. All patients will be required to complete written informed consent before enrolment. If patients are unable to complete written informed consent, it will be obtained from their relatives.

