### Sample size

2.9

This study is a RCT, and the diopter of the research object is the main observed outcome index. According to previous literature reports, it is estimated that the mean diopter of experimental group 1 is -1.52, the standard deviation is 0.87, and the diopter of experimental group 2 is- 1.81, the standard deviation is 1.25. Set α = 0.25 (2-sided) and β = 0.10. We use PASS 15 software (PASS 15.0.5 NCSS, LLC USA) to calculate the experimental size of the test group and the control group N1 = N2 = N3 = 74 cases. Assuming that the loss to follow-up rate of the study subjects is 20%, the sample size is N1 = N2 =  = N3 = 74÷0.8 = 93 cases. Therefore, the minimum sample size included in this study is 279 cases. In the actual study, a total of 300 cases will be included.

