### Randomization and allocation concealment

2.10

Central random system is used to realize random grouping and random hiding of hierarchical blocks. This study is stratified according to the subcenter, randomly divided into acupuncture Deqi group, acupuncture without Deqi group, and waiting list group at a ratio of 1:1:1. A statistician from Sichuan Evidence-based Medicine Center of Traditional Chinese Medicine will use SAS 9.2 software (SAS, Cary, NC) to generate random sequences in 3 rounds of random sentences, list the random code tables corresponding to the serial numbers 001–300, and generate treatment assignments for 300 subjects. This process is implemented by the online central random system. The researcher enters the screening information of the prospective subjects on the central random system and obtains the subject number. After meeting the subject's criteria and signing the informed consent form, they are randomly divided into groups, and the random number is generated. Examiners and researchers cannot foresee the grouping information of the subjects, and the random number is managed by Sichuan Evidence-based Medicine Center of Traditional Chinese Medicine. Until the end of the study, the subjects, clinicians, and outcome measurers did not know the grouping of subjects.

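### As written, the two needle arms differ in insertion angle as well as in manipulation, so followed literally the Deqi contrast cannot be separated from angle

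*Protocol article*

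**What the plan says.** All references are to the protocol article.

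- **Section 2.12.2 (Deqi arm):** after naming the three points around the eye and the needle, the instruction is "use both hands to insert the needle, flat puncture to deqi, lift and twist, 20 to 30 min/time".
- **Section 2.12.3 (without-Deqi arm):** to avoid the Deqi response, "no needle manipulation will be performed after the perpendicular insertion". The next sentence adds that "all the rest of the clinical procedures remain the same".
- **Section 2.2 (Study design):** "acupuncture without Deqi group will be treated with acupuncture, but no needle manipulation will be performed". No angle is mentioned for either arm.
- **Abstract, Methods:** the comparator is described as not being given flat puncture to Deqi. The negation can attach to the flat puncture or to the Deqi.
- **Introduction:** "Deqi is a complex cluster of sensation evoked by acupuncture stimulation". The stated aim is to "compare the curative effect of acupuncture for Deqi and acupuncture without Deqi in adolescent patients with myopia".
- **Section 2.16** tests the two needle arms against each other through a time-by-intervention interaction. **Section 3** calls that contrast the specific effect, and calls the contrast of without-Deqi with waiting list the nonspecific one.
- **Section 2.11 (Blinding)** mentions pseudo-acupoints but assigns them to no arm.

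**The concern.** The comparison of the two needle arms carries the trial's main question. To be read as the effect of Deqi, the arms should differ only in what produces or withholds Deqi. By the Introduction's definition that is stimulation and the sensation it evokes. Sections 2.2 and 2.12.3 agree with this, since both make withholding manipulation the means of avoiding Deqi. But the intervention text also gives the arms different insertion angles, and no section explains why.

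Randomisation does not deal with this, because angle is part of the assigned treatment and not a patient characteristic. What is at stake is attribution: a difference between the needle arms could reflect angle, manipulation or both, while section 3 would assign it to Deqi alone.

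**Working it through.** The plan gives no figure for this point, so the check compares the texts and then asks what the data could identify.

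**Step 1. The two instructions side by side**

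| Element | Deqi arm (2.12.2) | Without-Deqi arm (2.12.3) |
|---|---|---|
| Insertion | flat | perpendicular |
| Manipulation | lifting and twisting, to Deqi | none |
| Everything else | 20 to 30 minutes; Sizhukong, Tongziliao, Sibai | stated to be unchanged |

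Two rows differ. Section 2.2 accounts for only the second.

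**Step 2. Does any text restore a common angle?**

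- The statement in section 2.12.3 that the remaining procedures are unchanged follows directly on the explicit perpendicular insertion. It covers the rest and does not override what has just been specified.
- Section 2.2 is silent on angle.
- The abstract, read as denying flat puncture, confirms that the angles differ. Read as denying Deqi, it says nothing about angle. Neither reading gives equal angles.

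**Step 3. Numbers involved**

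Inputs: "In the actual study, a total of 300 cases will be included" (section 2.9), and allocation to the Deqi group, "acupuncture without Deqi group, and waiting list group at a ratio of 1:1:1" (section 2.10).

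- Per arm: 300 / 3 = 100. Needled participants: 2 × 100 = 200.
- At the stated minimum of 279: 279 / 3 = 93 per arm, and 2 × 93 = 186 needled.

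If the text is followed literally, the 200 fall as follows.

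| | Manipulated to Deqi | Not manipulated |
|---|---|---|
| Flat | 100 | 0 |
| Perpendicular | 0 | 100 |

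**Step 4. What the contrast estimates**

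Write M for the effect of manipulation to Deqi and A for the effect of flat rather than perpendicular insertion, and suppose for simplicity that they add. Then:

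- Deqi minus without-Deqi = M + A.

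The contrast equals M only if A = 0. With the off-diagonal cells empty, the indicator for angle and the indicator for arm are the same variable, so a model containing both cannot be fitted. Covariate adjustment does not help, because angle does not vary within an arm. The waiting-list arm does not help either, because it receives no needling.

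These counts show that angle and arm coincide completely. They carry no information about the size of A.

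**The case against.** **The angle may be a disclosed part of the technique.** On one natural reading of the abstract, flat puncture belongs to the Deqi technique and its absence belongs to the comparator. This is a fair reading, and the difference would then be deliberate. It does not settle the matter. The abstract's sentence has another reading, section 2.2 names manipulation only, and no section says that perpendicular insertion was chosen to avoid Deqi. Even if the difference is intended, the conclusion in section 3 would be worded too narrowly, since the arms would differ in a combined technique.

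**Perpendicular may be a drafting slip.** This is plausible. Section 2.12.3 refers to the perpendicular insertion as though it had already been described, presents the absence of manipulation as the means of avoiding Deqi, and then says the rest is unchanged. All of that fits an intended common insertion with one wrong adjective. If so, the problem disappears once the word is corrected. Nothing in the article corrects it, however, and it stands in the section that tells the acupuncturist what to do.

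**Operating detail may sit elsewhere.** The article is condensed, and section 2.11 refers to uniform standards that are not shown. This limits any inference about how needles will actually be placed. The point does not rest on missing detail, though: both angles are stated.

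**No effect of angle is shown.** Correct. The article gives no reason to expect angle alone to change refraction, and no basis for a size or direction.

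**Stronger readings that the text does not support.** A reader might infer that the Deqi comparison is biased. The article shows only that a bias is possible and that, if present, it could not be removed in analysis. A reader might also infer from section 2.11 that the comparator is needled at sham points. The term is attached to no arm, and section 2.12.3 implies the same points in both needle arms, so it supports only a request to clarify.

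**Conclusion.** The point holds as an inconsistency in the intervention text with a conditional consequence. If sections 2.12.2 and 2.12.3 are followed literally, angle and arm coincide in 200 of 200 needled participants (186 of 186 at the stated minimum), and the contrast that section 3 calls the specific effect of Deqi cannot be told apart from an effect of angle.

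The conclusion assumes that flat and perpendicular mean different angles and that the acupuncturist works to the text as printed. It does not assume that angle affects diopter: the possible error in the Deqi estimate has unknown size and direction, and may be zero. No sample size, error rate or power figure changes. The correction is worth making because it protects the trial's main comparison at almost no cost, and because the ambiguity cannot be resolved by analysis afterwards.

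**What to change.** 1. In sections 2.12.2 and 2.12.3, give both needle arms the same insertion angle and name the same three acupoints (Sizhukong, Tongziliao, Sibai), so that only manipulation to Deqi differs. Bring the sentence in the abstract into line.
2. If the angle difference is deliberate, say so and give the reason in sections 2.2 and 2.12.3. Then word the conclusion as a comparison of two needling techniques and not as the effect of Deqi alone.
3. In section 2.11, state what pseudo-acupoints refers to, or bring the sentence into agreement with section 2.12.3. Simply deleting the term would presume that it is wrong.

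The cost is protocol wording and acupuncturist instruction, with no change to sample size, visits or analysis. Under the second option the price is a narrower conclusion.
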